### 3. TREATMENT OF SUBJECTS

#### 3.1 Investigational product/treatment

##### Intervention

The CBTsa therapy is based on accumulating evidence that dysfunctional beliefs in conjunction with neurocognitive impairments can impede functioning [3]. The core assumption of this therapy is that modifying dysfunctional beliefs will lead to increased engagement in constructive social activity in individuals with prominent negative symptoms [7]. Its primary focus is to help participants overcome isolation and inactivity, and thereby improve quality of life [2], rather than focusing primarily on reduction of psychotic symptoms. CBTsa will target several defeatist beliefs and defeatist performance attitudes (e.g. 'if you cannot do something well, there is little point in doing it at all'). Apart from defeatist beliefs focusing on personal skills (such as cognitive functioning), negative expectancies regarding one's ability to experience pleasure (low anticipatory pleasure: 'I will not be able to enjoy this') are often reported by patients with schizophrenia. These types of beliefs combined with asocial beliefs (e.g. 'having close friends is not as important as most people say') have been found to result in (social) withdrawal and inactivity.

In the current intervention, Cognitive behavioural techniques will focus primarily on correcting these dysfunctional beliefs about pleasure, cognitive abilities, performance and social functioning. The intervention will consist of a group-based and an individual part, combining advantages of group processes and peer interaction with individual CBT. One major component of the group-based part is peer support (sharing experiences & practicing skills together with peers). The individual CBT sessions will be composed of personal case formulations, investigation of specific dysfunctional beliefs and behavioural experiments will be addressed.

In short, the intervention will constitute of:

1. Group sessions for 4 weeks, two sessions per week, 60 minutes per session, two trainers (a CBT therapist and a CBT assistant); eight participants, and;
2. Individual sessions (crystallizing learned skills, focus on individual needs) during 6-8 weeks, one session per week, 45 minutes per session.

The Group sessions (8 in total) will consist of:

Psycho-education, peer support, buddy-forming, social goal setting, breaking goals down into steps and planning them, find obstacles and dysfunctional cognitions, behavioural experiments, and imagery for executing goal steps.

The Individual Sessions will contain: Individual case formulations (including the person's main dysfunctional beliefs and associated behaviours), continuation of working on social goals and countering obstacles to these goals. Also, psycho-education about symptoms, the role of cognition / beliefs and consequences of current behaviour will be addressed. Specific cognitive techniques that will be used to investigate dysfunctional beliefs and behaviour are a.o. 'Socratic dialogue', behavioural and cognitive experiments; dimensional evaluation of negative or stereotype self image etc); cognitive imagery techniques (imagining the steps needed to achieve new goals); behavioural techniques (activity scheduling, exposure to new situations that trigger anxiety etc.). Finally family members / important others will be involved. The choice for a particular combination of the above mentioned techniques will be based on the individual needs and goals of the patients.

To ensure treatment engagement and adherence, sessions will be adapted to the particular group under study: young patients recovering from recent episode psychosis. Adaptations for specific subgroups of patients may include specific illness characteristics (for example cognitive problems; concentration), gender and ethnic background. For example, sessions will be kept as low-level as possible and adapted to specific interests of the adolescent group: attention will be paid to sharing experiences, guaranteeing an open and safe treatment atmosphere; 'fun' parts (such as social games) will be included in the program. Further, treatment session time and duration will be adapted to the needs of individual patients (for example shorter en more frequent sessions). We will strive to address diversity (regarding age, gender, ethnic background etc) in the group- based part of the intervention as well as the individual part, for example by involving family members or important others to discuss implementation of treatment gains in patient's daily life.

### Standard treatment (ST)

Participants in both study conditions will receive ST. Participants are hospitalized or attending day-treatment at the Department of Early Psychosis, Amsterdam, the psychosis department of the ABC team, Utrecht, Parnassia Den Haag and collaborating (local community) mental health centers.

At minimum, Standard Treatment consists of antipsychotic medication and supportive therapy. Additional components of standard care for patients with psychotic disorders are psycho education, family support, physical health care, psycho motor therapy and vocational therapy.

### **3.2 Use of co-intervention (if applicable)**

All participants are allowed to use antipsychotic medication, as part of their ST.

## **4. METHODS**

### **4.1 Study parameters/endpoints**

#### **4.1.1 Main study parameter/endpoint**

For comparison reasons and in congruence with earlier work ([name] et al., available on request), our primary outcome measure will constitute of a negative symptom sum score (see 5.3. study procedure). In addition, we will look separately at one of the specific impact of our intervention on withdrawal behaviour.

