## SUMMARY

**Rationale:** There is growing consensus that targeting negative symptoms such as social withdrawal is essential to be able to preserve social participation, thereby reducing the high yearly costs of schizophrenia. Aaron T. Beck, founder of Cognitive Behavioural Therapy (CBT), and colleagues have developed and investigated a new CBT approach, in which they target inactivity in a chronic schizophrenia population with severe negative symptoms. The therapy is based on accumulating evidence that dysfunctional beliefs in conjunction with neurocognitive impairments can impede social functioning. These results suggest that CBT can be highly successful in establishing clinically meaningful improvements. However, the therapy has not yet been investigated in a recent-onset population.

**Objective:** To evaluate the applicability and (cost-) effectiveness of a shortened, partly group based, Cognitive Behavioural Therapy focussing on social activation (CBTsa) in patients with recent onset schizophrenia.

**Hypotheses:** 1) We hypothesize that CBT focused on social activation (CBTsa) in a recent-onset population will result in a substantial reduction in severity of negative symptoms, in particular social withdrawal.

2) We expect that CBTsa will lead to an improvement in terms of Quality of Life and overall functioning.

3) We expect this intervention to result in a reduction in need for care and QALY gain as a consequence of improvement in symptoms and social functioning.

**Study design:** Single blind randomized controlled trial with 6 month-follow up.

**Study population:** Patients between 18 and 35 years old with negative symptoms of at least moderate severity, and who have been recently (< 2yrs) diagnosed with schizophrenia.

**Intervention (if applicable):** Individual and group-based CBT intervention targeting social withdrawal.

**Main study parameters/endpoints:** Change in negative symptoms, Social functioning, and quality of life, Productivity losses.

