### **2.4 Sample size calculation**

The effectsize to calculate our estimated sample size is based upon a recent groundbreaking study of Grant and colleagues (one of our co-applicants), who carried out an intervention with

similar ingredients as ours in a more chronic schizophrenia population. In their study, also specifically targeted to reduce negative symptoms and to socially activate their patient sample, they found that patients receiving cognitive therapy showed a greater mean reduction in avolition-apathy (adjusted mean [SE], 1.66 [0.31] vs 2.81 [0.34], respectively;  $P=.01$ ; between-group  $d=-0.66$ ) as compared with those receiving standard treatment. This outcome measure is comparable to the 'social withdrawal' outcome measure used in our study. Based on this results, and upon the commonly hold assumption that recent onset subjects are more likely to change than the more chronic population, we estimated to find an effectsize of (at least) .66 in our study as well. With an alpha of 0.5; power=80%; effect-size .66 [3], this would mean we need 36 participants per group to detect a true treatment difference. Taking into account an expected dropout rate of 20%, we would need to include  $72 + 20\% = 87$  participants = 44 per group.

To take into account the 'variance inflation' factor (due to our multi-center design), we calculated the Intra Class Correlation Coefficient of the PANSS negative symptom scores of a study targeting a similar population and setting (GROUP), in which 4 centers participated. The ICC in this study was .146. Following the literature, we then used the following formula:  
 $1 + (m-1) \times \text{ICC}$  (m= number of participating centers).

For our study this means we have to increase the sample size (87) by a factor of:

$$1 + (3-1) \times .146 = 1.292$$

This results in a total estimated sample size of:  $1.292 \times 87 = 112$  individuals (56 per condition)

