#### **4.1.2 Secondary study parameters/endpoints (if applicable)**

Quality of Life, Global Functioning, Productivity losses, Severity of symptomatology, Need for Care

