**Table 1. Test battery**

| Primary outcome          | Instruments                                                                                   | Characteristics Instrument                                                                                                                                                                                                                                                                                                                                                                                                                                                                                                                                    |
|--------------------------|-----------------------------------------------------------------------------------------------|---------------------------------------------------------------------------------------------------------------------------------------------------------------------------------------------------------------------------------------------------------------------------------------------------------------------------------------------------------------------------------------------------------------------------------------------------------------------------------------------------------------------------------------------------------------|
| Negative symptoms        | Negative symptom domain of the Positive and Negative Syndrome Scale (PANSS; Kay et al., 1986) | Consists of 7 item clusters and produces a total score ranging from 7 (minimum) to 49 (maximum).                                                                                                                                                                                                                                                                                                                                                                                                                                                              |

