|                          | Brief Negative Symptom Scale [BNSS; 10]:                                                      | Assesses objective and self-perceived negative symptoms and to be used in clinical trials [11]. 13 items that can be rated in a 15-minute interview. In contrast to other scales, the scale includes separate items for internal experiences and outward behaviour for asociality amongst others. Reliability analyses indicate that the BNSS has excellent internal consistency and temporal stability [11]. This scale has recently been officially translated by our research group by means of the back-forward translation method (article in progress). |
|                          | Experience Sampling Method (ESM [9]) currently transformed into a smartphone device:          | Structured self-assessment technique ESM will be used to examine frequency of real-life activity and situational, cognitive, affective and behavioural aspects that precipitate social withdrawal. In contrast to the commonly used questionnaires, ESM not only yield more ecologically valid measures of social behaviour; it is also more attractive for the young target group, increasing the feasibility of the study.                                                                                                                                  |
| Secondary Outcome |                                                                                               |                                                                                                                                                                                                                                                                                                                                                                                                                                                                                                                                                               |

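### The protocol does not settle which outcome is primary, and its sample size rests on an effect for a different measure from the sum score it declares

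*Protocol*

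**What the plan says.** Four places in the protocol bear on the primary outcome.

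- **Section 4.1.1** is in the singular: "our primary outcome measure will constitute of a negative symptom sum score (see 5.3. study procedure"). It names no scale. It then adds withdrawal as a further look: "In addition, we will look separately at one of the specific impact of our intervention on withdrawal behaviour".
- **Table 1**, in the study procedures, has three entries under the primary outcome: "Negative symptom domain of the Positive and Negative Syndrome Scale" (total 7 to 49), "Brief Negative Symptom Scale [BNSS; 10" (13 items), and "Experience Sampling Method (ESM [9]) currently transformed into a smartphone device". The ESM entry concerns how often real-life activity occurs and what precedes withdrawal.
- **The Summary** gives the main endpoints as "Change in negative symptoms, Social functioning, and quality of life, Productivity losses". Section 4.1.2 lists as secondary "Quality of Life, Global Functioning, Productivity losses, Severity of symptomatology, Need for Care". Table 1 also puts quality of life and productivity losses under the secondary outcomes.
- **Section 2.4** takes d = 0.66 from an earlier trial's result on avolition-apathy in a more chronic population, and says of it: "This outcome measure is comparable to the 'social withdrawal' outcome measure used in our study". The ICC of 0.146 in the same calculation comes from PANSS negative symptom scores.

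Section 5.3 plans a repeated-measures mixed model for negative symptoms over time and names no scale.

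**The concern.** A reader of the protocol cannot say which result decides whether the trial succeeded. Section 4.1.1 allows one score, Table 1 offers three instruments, and the Summary offers four domains, at least two of which are secondary elsewhere. If this stands, the main claim could rest on whichever listed instrument turns out favourably, while the sample size was built for a single test.

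The second part concerns power. The effect size is tied to social withdrawal, which section 4.1.1 treats only as an addition to the primary. The 80% power therefore belongs to a measure other than the declared one, and the protocol offers no argument that 0.66 also applies to a broader negative symptom sum score.

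**Working it through.** **1. Which outcome is primary**

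| Place | What it makes primary or main | Conflict |
|---|---|---|
| 4.1.1 | One negative symptom sum score, scale not named | Cites 5.3, which is the statistical section and names no scale |
| Table 1 | PANSS negative, BNSS, ESM | Three instruments against one score; ESM is not a symptom sum score |
| Summary | Negative symptoms, social functioning, quality of life, productivity losses | Quality of life and productivity losses are secondary in 4.1.2 and Table 1 |
| 2.4 | Powered on social withdrawal (through avolition-apathy) | 4.1.1 treats withdrawal as an additional look |

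The words attached to the cross-reference point to the study procedures, which the table of contents numbers 4.3 and which contain Table 1. Following the words and not the number leads to three instruments, so the scale remains open on either reading.

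**2. Reproducing the sample size**

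Inputs from section 2.4: d = 0.66, power 80%, dropout 20%, ICC 0.146, three centres. Alpha is printed as 0.5. The stated result is reproduced only with 0.05 two-sided: 0.5 would give 11 per group, and one-sided 0.05 would give 29.

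- n per group = 2 × ((1.960 + 0.842) / 0.66)² = 36.04; the protocol states 36.
- Dropout as the protocol applies it: 72 × 1.2 = 86.4, rounded up to 87.
- Inflation: 1 + (3 − 1) × 0.146 = 1.292, and 87 × 1.292 = 112.4; the protocol states 112.

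The calculation is thus for one two-sided test of one outcome at d = 0.66. It contains no allowance for more than one primary measure.

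**3. Error if each listed instrument were tested**

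Assumption: each instrument is tested once, two-sided at 0.05, and a success on any one counts. For k independent tests the family-wise error is 1 − 0.95^k. For correlated tests it is the probability that at least one of k equally correlated normal statistics exceeds 1.96 in absolute value.

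| Correlation | Two sum scores (PANSS negative, BNSS) | Three instruments |
|---|---|---|
| 0 | 9.8% | 14.3% |
| 0.3 | 9.5% | 13.6% |
| 0.5 | 9.1% | 12.5% |
| 0.7 | 8.3% | 10.9% |
| 0.9 | 7.0% | 8.4% |

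The protocol gives no correlations, so the whole range is shown.

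**4. Power if the effect on the sum score is smaller**

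The basis is the protocol's own 36 evaluable per group, that is, the number left once its dropout and centre inflation are taken back out: 112 / 1.292 / 1.2 / 2 = 36.1. Two-sided t-test at 0.05:

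| d | Power |
|---|---|
| 0.66 (section 2.4) | 79% |
| 0.5 (assumed) | 55% |
| 0.4 (assumed) | 39% |

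The 79% differs from the stated 80% only because the t distribution is used; the normal approximation gives 80.0%.

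**The case against.** The best defence is that a likely primary can be recovered from the text. Section 4.1.1 is in the singular, and ESM cannot be a symptom sum score. PANSS negative is the only Table 1 primary entry described as producing a total, and the same scale supplies the ICC in section 2.4, the treatment response in the cost-effectiveness analysis and the effect in the net-benefit regression. On this view the fault is one of labelling. This has force, and it is why PANSS negative is the natural candidate. It remains an inference: Table 1 gives BNSS and ESM the same primary heading, and a 13-item scale can also be summed.

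A reader might go further and count three instruments at two follow-up assessments as six tests, with a family-wise error of up to 26.5%. The protocol does not support that. It states no rule that success on any measure at any visit suffices, and section 5.3 plans a mixed model over time, not separate tests per visit. The primary time point or contrast may be fixed in the SAP, which is not shown.

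A reader might also take 56 × 0.8 = 44.8 completers per group and report 87% power at d = 0.66. That drops the protocol's own factor of 1.292 and is not its basis.

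Finally, section 2.4 openly says that 0.66 comes from avolition-apathy in a more chronic population and gives a reason for borrowing it. That disclosure stands. What it lacks is the step from social withdrawal to the declared sum score. Nothing in the document shows that the effect on the sum score is smaller; it only leaves the question unaddressed.

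**Conclusion.** The concern holds as a contradiction within the protocol. Section 4.1.1, Table 1, the Summary and section 4.1.2 cannot all be followed, and the power statement belongs to a measure other than the declared primary. This goes beyond detail that could be left to a SAP, because the passages disagree with one another about the choice of primary outcome.

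Its size is moderate. Against a nominal 5%, the family-wise error is about 7-10% for two sum scores and 8-14% for three instruments, provided each is tested once at 0.05 and any success counts, over correlations from 0.9 to 0. Power falls from about 79% to 55% or 39% only if the effect on the sum score is 0.5 or 0.4, which are assumed values. The missing primary time point is not part of this finding.

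**What to change.** - In section 4.1.1, name one scale and one score as primary. The PANSS negative total (7 to 49) is a reasonable example, since it already supplies the ICC and the cost-effectiveness response. Correct the cross-reference.
- In Table 1, move BNSS and ESM to the secondary outcomes, and list social withdrawal there too.
- In the Summary, keep only the chosen score as the main endpoint. In section 5.3, name the same score in place of negative symptoms in general.
- In section 2.4, state that 0.66 is assumed to carry over from avolition-apathy to the chosen sum score, and give power at smaller effects with 36 evaluable per group (the figures above would serve).

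The cost is a protocol amendment in wording, made before unblinding. No assessment or procedure changes, and 112 can stay if the 0.66 assumption is kept. The price is that the other instruments can no longer carry the main claim.

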#### **4.1.2 Secondary study parameters/endpoints (if applicable)**

Quality of Life, Global Functioning, Productivity losses, Severity of symptomatology, Need for Care

#### **4.1.3 Other study parameters (if applicable)**

Substance Use, (socio-) demographic characteristics

### **Study procedures**

After the participants have read and signed informed consent, and before treatment allocation, all patients will undergo a two hour during test battery carried out by an academic research assistant. Afterwards, participants will be asked to carry along an electronic device/ with an application with which participants are prompted by a beep at random intervals throughout the day (for a 6-day period) to report about their current experiences and withdrawal behaviour (see Experience Sampling Method (ESM; 9) table 1). The test battery will be repeated at the end of treatment, and 6-months post- treatment.

Patients allocated to the CBTsa condition will receive group sessions for 4 weeks, and 6-8 weeks weekly individual CBT sessions (see above).

**Table 1. Test battery**

| Primary outcome          | Instruments                                                                                   | Characteristics Instrument                                                                                                                                                                                                                                                                                                                                                                                                                                                                                                                                    |
|--------------------------|-----------------------------------------------------------------------------------------------|---------------------------------------------------------------------------------------------------------------------------------------------------------------------------------------------------------------------------------------------------------------------------------------------------------------------------------------------------------------------------------------------------------------------------------------------------------------------------------------------------------------------------------------------------------------|
| Negative symptoms        | Negative symptom domain of the Positive and Negative Syndrome Scale (PANSS; Kay et al., 1986) | Consists of 7 item clusters and produces a total score ranging from 7 (minimum) to 49 (maximum).                                                                                                                                                                                                                                                                                                                                                                                                                                                              |
|                          | Brief Negative Symptom Scale [BNSS; 10]:                                                      | Assesses objective and self-perceived negative symptoms and to be used in clinical trials [11]. 13 items that can be rated in a 15-minute interview. In contrast to other scales, the scale includes separate items for internal experiences and outward behaviour for asociality amongst others. Reliability analyses indicate that the BNSS has excellent internal consistency and temporal stability [11]. This scale has recently been officially translated by our research group by means of the back-forward translation method (article in progress). |
|                          | Experience Sampling Method (ESM [9]) currently transformed into a smartphone device:          | Structured self-assessment technique ESM will be used to examine frequency of real-life activity and situational, cognitive, affective and behavioural aspects that precipitate social withdrawal. In contrast to the commonly used questionnaires, ESM not only yield more ecologically valid measures of social behaviour; it is also more attractive for the young target group, increasing the feasibility of the study.                                                                                                                                  |
| Secondary Outcome |                                                                                               |                                                                                                                                                                                                                                                                                                                                                                                                                                                                                                                                                               |
| Quality of Life          | EQ-5D-5L; 12                                                                                  | To assess (changes in) quality of life we will make use of the EuroQol (EQ-5D-5L).                                                                                                                                                                                                                                                                                                                                                                                                                                                                            |
| Global functioning       | Global Assessment of Functioning Scale (GAF [13]).                                            | This scale is rated on a scale from 1 to 100, for the current situation and for highest level in past year. 1 to 10, for example, signifies 'a persistent danger of severely hurting self or others (e.g., recurrent violence) OR persistent inability to maintain minimal personal hygiene OR serious suicidal act with clear expectation of death', whereas 91 to 100 on the other hand, stands                                                                                                                                                             |

|                                     |                                                                                        |                                                                                                                                                                                                                                                                                                                                                                                                                                                                                                                                                                                                                                  |
|-------------------------------------|----------------------------------------------------------------------------------------|----------------------------------------------------------------------------------------------------------------------------------------------------------------------------------------------------------------------------------------------------------------------------------------------------------------------------------------------------------------------------------------------------------------------------------------------------------------------------------------------------------------------------------------------------------------------------------------------------------------------------------|
|                                     |                                                                                        | for 'Superior functioning in a wide range of activities.., no symptoms.'                                                                                                                                                                                                                                                                                                                                                                                                                                                                                                                                                         |
| Productivity losses                 | SF-HLQ [14]                                                                            | Effects on ability to perform paid and unpaid work                                                                                                                                                                                                                                                                                                                                                                                                                                                                                                                                                                               |
| Positive and General Symptomatology | PANSS [8]                                                                              | The PANSS is currently the most widely used scale to assess the severity of a variety of symptoms in patients with schizophrenia. Originally the PANSS consists of three sub scales: positive syndrome scale (item P1–P7), a negative syndrome scale (items N1–N7) and general psychopathology scale (item G1–G16).                                                                                                                                                                                                                                                                                                              |
| Depression                          | Calgary Depression Scale for Schizophrenia (CDSS [15])                                 | Nine-item scale specifically designed for schizophrenic patients that permits evaluation of depression independently from extrapyramidal and negative symptoms [15].                                                                                                                                                                                                                                                                                                                                                                                                                                                             |
| Inhibition/ Activation              | Behavioural Inhibition/ Behavioural Activation Scales (BISBAS [16])                    | a 20-item self-rating questionnaire with good psychometric properties. Comprises 7 BIS items and 13 BAS items. Each item has 4 response options ranging from 1 (strongly agree) to 4 (strongly disagree). Aims to examine individual differences in the sensitivity for one of the two motivational systems that underly behaviour: A behavioral approach system (BAS) is believed to regulate appetitive motives, in which the goal is to move toward something desired. A behavioral avoidance (or inhibition) system (BIS) is said to regulate aversive motives, in which the goal is to move away from something unpleasant. |
| Need for care                       | Camberwell Assessment of Need (CAN) [17].                                              | Includes 22 items (e.g. daytime activities, psychotic symptoms). All CAN items can be scored 0 (no problem), 1 (there was a problem, but the problem is met), 2 (unmet need) with a reference period including the last 3 months. The instrument is designed to measure all domains of need, a high level of internal consistency cannot be expected, but reliability has been reported "acceptable".                                                                                                                                                                                                                            |
| Possible confounders         |                                                                                        |                                                                                                                                                                                                                                                                                                                                                                                                                                                                                                                                                                                                                                  |
| Substance use                       | Cannabis Experience Questionnaire ( www.eu-gei.eu ) | Assessing (experiences caused by) all kinds of drug use in detail (DiForti and colleagues, developed for the multi-centered EU-Gene-Environment Interaction study,                                                                                                                                                                                                                                                                                                                                                                                                                                                               |
| Socio-demographics                  | Socio-Demographic Schedule ( www.eu-gei.eu )        | Measure designed for EU-GEI to assess socio demographic characteristics                                                                                                                                                                                                                                                                                                                                                                                                                                                                                                                                                          |

